## Ethics and dissemination

### Ethical, legal and regulatory aspects

Ethical approval was granted by Northwest–Greater Manchester Central Research Ethics Committee (REC 23/NW/0242). The intervention is delivered at a maternity unit level, and aggregate primary outcome data are reported for all women giving birth in the care of participating maternity services.

Electronic health records (EHR) will be retrieved under section 251 approval from the Confidentiality Advisory Group in England and Public Benefit and Privacy Panel for Health and Social Care (HSC-PBPP) in Scotland. Routine EHR currently cannot be requested in Northern Ireland and so pseudonymised PPH specific data will be collected and no linkage performed. Information about the study is displayed throughout participating maternity units, and online, including how to opt out of use of EHR for research (England) or the OBS UK study (England and Scotland). In Scotland women who have a PPH of >1.5 L and/or receive a blood transfusion for PPH are given a leaflet about the trial explaining how to opt out. Routine EHR will be linked to individual-level PPH specific data to develop a de-identified PPH research dataset for each nation. Data sources include Hospital Episode Statistics, Maternity Services, Emergency Services, Community Services and from Scottish equivalents. This will allow in-depth analysis of clinical outcomes, demographic and obstetric variables, economic and psychological outcomes and process measures.

Informed consent is obtained for the psychological, economic and process evaluation questionnaires, surveys and interviews (see Patient Consent Form online supplemental file 2 for an example). Amendments to trial documents including the protocol will be reviewed by the sponsor and REC. The Centre for Trials Research (CTR) will issue the site with the latest version of the documents as soon as they become available.

### Data management

Full details of the data management plan are available from: https://fundingawards.nihr.ac.uk/award/NIHR152057. This includes details of how data and confidentiality will be protected in line with NHS and University guidelines.

### Data availability

Anonymised OBS UK data will be made available on reasonable request to the study management group.

### Monitoring

The clinical trial risk assessment has been used to determine the intensity and focus of central and on-site monitoring activity in the OBS UK trial. Moderate monitoring levels will be employed (online supplemental file 5).

### Protocol deviation

Failure to fully implement or abandoning one of the components of the care bundle will not be regarded as a protocol deviation, however, if a site decides that an element of the bundle cannot be implemented at all this would be a protocol deviation and they will be withdrawn from the study. Implementation will be graded and considered as a sensitivity analysis. Appropriate obstetric care is permitted as per local guidance. Any additional trials at participating sites related to PPH or anaemia management must be discussed with CIs prior to consideration of inclusion.

A maternity unit starting to use a point-of-care device (ROTEM or TEG) located on the unit during the usual care period would make the unit ineligible and so would be considered a protocol deviation. If this were to happen then the unit would not be withdrawn and would be included in the planned analysis, using a treatment policy strategy.

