### Data analysis and statistics

#### Sample size

##### Primary outcome

The anticipated reduction in RBC transfusion from 27.5 to 18.0 per 1000 maternities is based on the effect size seen in the OBS Cymru pilot study and recently published UK PPH transfusion rates.^9
23^ The average unit size was anticipated to be about 3000 maternities per year.^35^ A stepped wedge cluster randomised trial (using maternity units as clusters) recruiting over 30 months, with 6 sequences and an estimated average of 750 maternities per 3-month period per unit, requires 5 units to be randomised to each sequence. The total of 30 units gives 93% power to detect the above effect size, based on a two-sided type I error rate of 5% and assuming a ‘discrete-time decay’ correlation structure with intra-class correlation of 0.002 (based on previous audit data and similar studies,^36^ and cluster auto-correlation of 0.80 while assuming no data from the 9-month implementation phase will be included in the analysis). With data from implementation months 5–9 included in the analysis (reflecting an assumption that transition to OBS UK care will be underway after 4 months) we will have 90% power to detect a reduction in the primary outcome from 27.5 to 22.0 RBC transfusions per 1000 maternities. The computations were performed using the Shiny CRT Calculator.^37^ One additional unit per sequence will be randomised (total of 36 units) to account for potential drop-out. Based on a more recent estimate of average maternity unit size of 3500 maternities per year, this corresponds to approximately 270 000 maternities to be included in the analysis. The primary outcome is collected monthly from each site using aggregate data and we do not anticipate missingness within the dataset.

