### Main analysis

Clinical and sociodemographic characteristics of women in participating maternity units as well as unit characteristics will be summarised descriptively and graphically.

The primary analysis will be intention-to-treat, meaning that all participants will be analysed as receiving usual care or OBS UK care (including data from women in months 5–9 of the implementation period) according to the randomisation status of their obstetric unit, regardless of adherence to the intervention. The primary estimand will use a treatment policy strategy for intercurrent events. It will use a logistic mixed-effects regression model with cluster (maternity unit) and cluster-time interaction fitted as random effects, fixed effects for time period (to capture secular trends) and exposure status as well as fixed effects for the stratification variables (unit size and point-of-care device) to estimate the OR of receiving RBC transfusion for PPH between OBS UK care and usual care, presented as a point estimate with a two-sided 95% CI and p value. If the estimate favours OBS UK care and the 95% CI excludes one, effectiveness of the intervention will be concluded. Similar analyses will be performed for the secondary clinical and psychological outcomes with linear instead of logistic models used for continuous outcomes for which at least approximate normality can be assumed.

Sensitivity analyses may consider alternative correlation structures, secular trends that differ between (randomised groups of) units, and intervention effect heterogeneity across time and/or (randomised groups of) units.^39
40^ In a further sensitivity analysis, a marginal mean model will be fitted using generalised estimating equations with robust SEs instead of mixed-effects regression, allowing a more population-focused interpretation.^41^

Subgroup analyses will explore the impact of ethnicity and/or socioeconomic factors and other aspects of demographic diversity on the intervention effect, by adding interaction terms with intervention to the analysis model.

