If some units implement individual elements of the OBS care bundle prior to entering the 9-month implementation period, or if individual units fail to implement the intervention during the 9-month period, this will be modelled in a separate sensitivity analysis. No unit will have adopted the point-of-care tests of coagulation or used QI methods for implementation of the entire OBS UK care bundle prior to the 9-month implementation period. The variation in prior adoption and/or partial implementation of individual elements will also be measured and considered in the process evaluation. The process evaluation will include exploring the role of sociodemographic and ethnic differences in staff and patient populations and build on the principles of equality, diversity and inclusion (EDI) in the analysis. A combination of Normalisation Process Theory and the Consolidated Framework for Implementation Research will be used to analyse data.^42
43^ Currently, neither framework attends explicitly to intersectionality nor EDI concerns, but these theories will be developed in this regard.

A statistical analysis plan will be agreed and signed off prior to database lock. Reporting of results will follow the Consolidated Standards of Reporting Trials (CONSORT) statement and its extension to stepped wedge cluster randomised designs.^44^

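### Withdrawing a site that decides a bundle element cannot be implemented at all conflicts with the intention-to-treat, treatment-policy primary analysis

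*Protocol article*

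**What the plan says.** Four statements in the protocol article bear on a unit that does not deliver the bundle.

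- **Main analysis, population and estimand.** The primary analysis is intention-to-treat: women are analysed "according to the randomisation status of their obstetric unit, regardless of adherence to the intervention". The same paragraph adds: "The primary estimand will use a treatment policy strategy for intercurrent events".
- **Main analysis, failure to implement.** The article states that "if individual units fail to implement the intervention during the 9-month period, this will be modelled in a separate sensitivity analysis".
- **Protocol deviation, first paragraph.** The milder case is tolerated: "Failure to fully implement or abandoning one of the components of the care bundle will not be regarded as a protocol deviation". The extreme case is not: "if a site decides that an element of the bundle cannot be implemented at all", then "this would be a protocol deviation and they will be withdrawn from the study". Implementation is also to be graded for a sensitivity analysis.
- **Protocol deviation, second paragraph.** If a unit starts using a point-of-care device on site during usual care, it becomes ineligible and this counts as a deviation, yet "the unit would not be withdrawn and would be included in the planned analysis, using a treatment policy strategy".

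The Sample size section randomises one extra unit per sequence (36 rather than 30) to cover drop-out, and expects no missing data in the monthly aggregate primary outcome. The article nowhere says what happens to the data of a withdrawn unit.

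**The concern.** The trigger for withdrawal is a site's own decision, taken after randomisation, about whether it can deliver the intervention. Losing a unit for that reason is not ordinary drop-out. A treatment-policy estimand asks what happens to transfusion rates when units are assigned to adopt OBS UK care, and inability to deliver part of the bundle belongs to that answer. If such units leave and their later outcomes are not collected, the estimate could move towards the effect among units that could adopt the whole bundle.

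The article already applies the treatment-policy principle to the mirror case. A unit contaminated during usual care is kept and analysed, while a unit that cannot deliver an element is withdrawn. The first kind of deviation tends to dilute the contrast and stays in. The second could also dilute it and is removed.

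**Working it through.** **Step 1: set the rules side by side.**

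| Situation | Status in the article | Where |
|---|---|---|
| Element partly implemented or abandoned | Not a deviation; unit stays; implementation graded | Protocol deviation, paragraph 1 |
| Unit fails to implement during the 9 months | Modelled in a sensitivity analysis | Main analysis |
| Site decides an element cannot be implemented at all | Deviation; unit withdrawn | Protocol deviation, paragraph 1 |
| Device used on the unit during usual care | Deviation; unit kept and analysed | Protocol deviation, paragraph 2 |
| Any non-adherence | Analysed as randomised; treatment policy | Main analysis |

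The third row cannot be followed together with the fifth unless outcome collection continues after withdrawal, which the article does not say. It also sits badly with the second row: a sensitivity analysis of units that failed to implement presumes that they are in the primary analysis. The same holds for implementation grading, since withdrawal would remove units at the bottom of the scale.

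**Step 2: what is lost at a minimum.** Suppose a withdrawn unit's earlier data are kept. Its outcomes from withdrawal onwards, under its randomised status, would still be missing, so the treatment-policy estimand would not be fully observed.

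**Step 3: a scale for the possible shift.** The article gives no expected number of such units and no effect size for them, so there is no plan figure to reproduce. The following is an illustration.

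Inputs from Sample size: 36 units, and a reduction from 27.5 to 22.0 per 1000, which is the scenario that includes implementation months 5–9, as the primary analysis does.

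Assumptions of mine: k affected units, equal weight per unit, no effect in those units, the full 5.5 per 1000 in the rest, and all data of withdrawn units dropped.

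- Effect with all units retained = 5.5 × (36−k)/36.
- Effect with those units withdrawn = 5.5.
- Inflation = 36/(36−k). This ratio does not depend on the 5.5.
- Odds ratio = [p/(1−p)] ÷ [0.0275/0.9725], where p = 0.0275 − effect/1000. With the units withdrawn, p = 0.022 and the odds ratio is 0.796.

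| k | Retained effect per 1000 | Retained OR | Withdrawn OR | Inflation |
|---|---|---|---|---|
| 1 | 5.5 × 35/36 = 5.35 | 0.801 | 0.796 | 36/35 = 1.029 |
| 3 | 5.5 × 33/36 = 5.04 | 0.812 | 0.796 | 36/33 = 1.091 |
| 6 | 5.5 × 30/36 = 4.58 | 0.829 | 0.796 | 36/30 = 1.200 |

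The absolute differences are 0.15, 0.46 and 0.92 per 1000.

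**Step 4: relax the zero-effect assumption.** If affected units kept half the effect, because the other elements were still delivered, the ratio becomes 36/(36 − k/2): 36/35.5 = 1.014, 36/34.5 = 1.043 and 36/33 = 1.091 for k = 1, 3 and 6.

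These are simple averages. The planned mixed model weights units and periods unequally and estimates a cluster-specific odds ratio, so the figures show scale only.

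**The case against.** The strongest reply is that being withdrawn from the study is not the same as being excluded from the analysis. The Main analysis section sets the analysis rule, and an analysis plan, to be signed off before database lock, may settle how a withdrawn unit's data are used. This stands in part. A reader might infer that such units' data are discarded, particularly because the next paragraph pairs not being withdrawn with being included in the analysis. That contrast is suggestive, but the article does not state exclusion. What remains is that the article positively prescribes withdrawal, and an unseen plan cannot analyse outcomes that were never collected.

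Second, the rule is narrow. Partial or abandoned implementation stays in, and local leadership support for implementing the intervention is an inclusion criterion for units. Few units may qualify. This limits the likely size but not the contradiction.

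Third, several stronger readings are tempting but unsupported.

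- That withdrawal can arise only on the intervention side: the trigger has no stated time limit, so a site could decide during usual care.
- That the rule removes the least responsive units: only one of four bundle components need be undeliverable, and nothing in the article shows that the effect would then be absent.
- That it breaks the constrained randomisation: unit size and device are adjusted for as fixed effects, and each sequence has a spare unit. Some loss of balance is possible, but breakage is not shown.

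Fourth, continued data collection is not free, because the local principal investigator decides whether each transfusion was for obstetric bleeding. This is correct and counts as a cost of the fix.

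**Conclusion.** The contradiction holds on the text alone and needs no figure. As written, the withdrawal rule cannot be reconciled with analysing units as randomised regardless of adherence, with handling failure to implement by sensitivity analysis, or with keeping units that have the mirror deviation. It is a post-randomisation loss linked to intervention delivery, and at least the later outcomes of affected units would go.

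The size is unknown. Under the illustrative assumptions (no effect in affected units, equal weights, all their data dropped) the inflation is about 3%, 9% and 20% for one, three and six units. A reader might take 9% to 20% as the expected bias. It is not: neither three nor six has a source in the article, and six would assign the whole drop-out allowance to this one trigger. With one unit, the odds ratio moves only from 0.801 to 0.796. A shift in favour of the intervention is plausible if such units respond less, but the article does not establish it.

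**What to change.** Reconcile the Protocol deviation and Main analysis sections. In place of withdrawal, state that:

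- the deviation is recorded;
- the unit's monthly aggregate primary-outcome data continue to be collected;
- the unit stays in the primary analysis under its randomised sequence;
- exclusion of the unit, or implementation grading, is used only in sensitivity analyses.

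The change is partly retrospective. Sequence 6 began implementation in August 2025, so its nine months ended around April 2026, before the article appeared in August 2026. The sponsor should therefore report whether any unit has been withdrawn under this rule and, if so, retrieve its aggregate counts. The trial runs to the end of January 2027 and the analysis plan is due before database lock, so there is time.

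The cost is a few sentences in the protocol and analysis plan. In any affected unit, the local judgement on whether each transfusion was for obstetric bleeding must also be continued or reconstructed. The estimate may be slightly less favourable than with those units removed, but it would then answer the question that the estimand poses.

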### Safety considerations

Since the components of the care bundle are recommended and used throughout the UK^8^ (although inconsistently), no adverse events are anticipated as a unique consequence of participation in the trial, and no expedited reporting of adverse events is planned. Maternal death and critical care admissions will be collected for all participants and monitored by the combined trial steering committee and Independent Data Monitoring and Ethics Committee.

If a woman receiving fibrinogen concentrate has an adverse drug reaction, the Medicines and Healthcare products Regulatory Agency (MHRA) will be informed using the Yellow Card scheme as per usual clinical practice, but these will not be reported as adverse events for the OBS UK trial. CSL Behring will be informed via email as described in the Pharmacovigilance Agreement if the MHRA is informed of any adverse drug reactions associated with Riastap supplied for study use.

All participants will be recruited at NHS sites and therefore the NHS indemnity scheme/NHS professional indemnity will apply with respect to claims arising from harm to participants at site management organisations.

### Patient and public involvement

Two women with lived experience of PPH from ethnic minority backgrounds are co-investigators. The research team, in collaboration with Egality Health, has facilitated workshops with organisations from under-represented communities to discuss patient-centred outcomes, advise on ethical issues (including consent and management of personal data) and develop communication materials to tackle unconscious bias, inform communities of the study and seek their endorsement. The workshops have also informed the establishment of an Advisory Group for the study who meet at least 6 monthly. The Advisory Group have influenced the psychological questionnaires, all public-facing materials and reviewed the plain English summary.

### Dissemination

The results of this study will impact policy and practice on a national and international level. To support rapid review of national guidelines and practice, results will be communicated to RCOG, Royal College of Anaesthetists, Royal College of Midwives and National Institute for Health and Care Excellence. The dissemination strategy and materials will be co-developed with our Patient and Public Involvement Advisory Group. Study outcomes will be published in peer-reviewed journals and presented at conferences and forums targeting key stakeholders including local maternity services.

## Discussion

The OBS UK trial includes a large nationally representative sample, robust stepped wedge cluster randomised design and comprehensive evaluation of clinical, psychological and economic outcomes within routine clinical settings. Some limitations should be considered. First, the OBS UK care bundle is being evaluated as a whole, meaning further studies will be needed to examine the individual components of the intervention. Additionally, the study is being conducted in a high-income country so generalisability to countries with lower economic status will be limited. Lastly, the use of more accurate and objective measurement methods may increase the number of PPH events detected compared with clinical estimation performed during usual care. Any observed increase in PPH incidence should therefore be interpreted in the context of improved ascertainment rather than a true increase in haemorrhage.

Overall, the OBS UK trial will generate comprehensive evidence to inform both clinical practice and future research aimed at improving outcomes for women experiencing PPH.

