24^ The OBS bundle consists of four interdependent components: risk assessment, QBL during and after all births, escalation of multiprofessional care to more senior staff at defined times and point-of-care testing of coagulation to guide targeted blood component replacement (online supplemental file 2 and online supplemental file 3).

The need for testing was informed by earlier work on fibrinogen, a key component of blood clots, which can fall to critically low levels before other clotting factors during PPH.^25^ Low fibrinogen is associated with placental abruption but may occur unexpectedly.^26^ Infusing coagulation products based on volume of PPH may be inappropriate when coagulation is normal.^11
26^ Fibrinogen >2 g/L is adequate for haemostasis during PPH, but laboratory results take over 1 hour to be available. Validated algorithms for two point-of-care devices, ROTEM and TEG, have been published and updated.^27
28^ Point-of-care coagulation tests provide clinicians with results in minutes, allowing early identification and correction of low fibrinogen levels with concentrated fibrinogen products (fibrinogen concentrate or cryoprecipitate) infused at a time and dose specific to the woman.^29^ This approach was integrated into the OBS Cymru PPH care bundle.

The OBS Cymru intervention was associated with a reduction in massive PPH by 1.10 (95% CI 0.28 to 1.92) per 1000 maternities per year (p= 0.011), but a full evaluation was not possible with the project design.^23^ A robust evaluation of the OBS care bundle requires comparison to usual National Health Service (NHS) care using a rigorous study design incorporating psychological and cost implications and investigating the impact of ethnic and socioeconomic diversity. A process evaluation will inform adoption and mechanisms of impact, ensuring that changes are fully assessed and learning can be applied to other healthcare settings.

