#### Secondary outcomes

##### Clinical

The following outcomes are reported as number from 4 hours before birth to hospital discharge, per 1000 maternities

Blood loss: >1 L, >1.5 L, >2 L, >2.5 L.Blood transfusion: transfused cell salvage and/or allogenic RBCs and the volume.Other blood components/products transfused: transfused coagulation products including type of product (fresh frozen plasma, cryoprecipitate, platelets or fibrinogen concentrate) and number of units or volume.Coagulopathy: fibrinogen levels <2 g/L, rotational thromboelastometry (ROTEM) Fibtem A5 <9 mm or thromboelastography (TEG) citrated functional fibrinogen (CFF) maximum amplitude (MA) (by 10 min) <17 mm, prothrombin time (PT)/ activated partial thromboplastin time (aPTT) >1.5× midpoint of normal reference range and platelet count <75×10^9^.

The following outcomes are reported as number from birth to hospital discharge, per 1000 maternities

Hysterectomy: due to PPH.Maternal death: following PPH.Higher level of care: level 2/3, high dependency or intensive care outside of the obstetric unit for complications following PPH.Cardiovascular shock: vasopressor infusion following PPH.Organ dysfunction: organ support following PPH.Haemostatic surgical and radiological interventions: uterine tamponade balloon insertion, uterine brace suture, transfer to theatre or any radiological intervention for PPH.

The following outcomes are reported as stated

Neonatal deaths and stillbirths: number, per 1000 maternities.Breastfeeding: time from birth to first feed, type (breastfeeding, formula, mixed), maintenance of breastfeeding including breast milk (only at 6 weeks).Mother and birth partner’s postnatal mental health, acceptability of and satisfaction with intervention, breastfeeding and adverse effects of intervention on mother, baby and birth partner: psychological quantitative study (described below).

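### The Discussion assigns any rise in recorded PPH to better measurement in advance, an inference the design does not support and which could hide a true rise in the blood-loss outcomes

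*Protocol article*

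**What the plan says.** Quantified blood loss is a component of the bundle: the Introduction lists "QBL during and after all births". The way blood loss is measured can therefore change when a unit moves from usual care to OBS UK care.

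Under Secondary outcomes, Clinical, four thresholds are outcomes per 1000 maternities: "Blood loss: >1 L, >1.5 L, >2 L, >2.5 L". Under Main analysis, "Similar analyses will be performed for the secondary clinical and psychological outcomes", and the primary result they are modelled on is "presented as a point estimate with a two-sided 95% CI and p value".

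The last limitation in the Discussion is that better measurement "may increase the number of PPH events detected compared with clinical estimation performed during usual care". The next sentence concludes: "Any observed increase in PPH incidence should therefore be interpreted in the context of improved ascertainment rather than a true increase in haemorrhage". It has no size limit, no condition on other outcomes and no reference to how the unit measured loss before. Nothing elsewhere in the article qualifies it.

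Two other places bear on the premise. The maternity-unit exclusion criterion removes only units that have taken up every part of the bundle, including a viscoelastic device on the obstetric unit. Main analysis foresees partial early uptake and plans a sensitivity analysis for it: "If some units implement individual elements of the OBS care bundle prior to entering the 9-month implementation period".

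**The concern.** The premise is a possibility and the conclusion is universal. Reading a rise in the light of improved ascertainment would be a fair caution; adding that it is not a true increase rules out the alternative before any data are seen.

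What is at stake is the interpretation of the four blood-loss outcomes. If bleeding truly rose under OBS UK care, the published interpretation would already have labelled the rise a measurement artefact. Safety considerations names maternal death and critical care admission for committee monitoring, and blood loss is not named there. That is a further reason not to discount a rise in advance.

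**Working it through.** No figure in the plan needs reproducing, because the statement rests on none. The check has three parts.

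**1. Does the conclusion follow from the premise?**

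- Premise (Discussion): quantification *may* raise detection relative to clinical estimation.
- Conclusion (Discussion): *any* increase is ascertainment and not haemorrhage.
- For the conclusion to hold, usual care would have to mean clinical estimation in every unit, and the measurement effect would have to account for the whole of any rise.
- The first condition is not secured. The exclusion criterion admits units using some elements, and Main analysis expects that some may adopt elements early. Main analysis rules out prior point-of-care coagulation testing and prior QI-led roll-out of the entire bundle; it does not rule out prior quantification. Where quantification was already in use, the instrument changes little.
- The second condition is not addressed. No accuracy is given for either method.

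**2. Can the observed rise separate the explanations?**

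Assume quantified loss detects 100% of true events and clinical estimation detects a share s. These sensitivities are assumptions.

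Observed ratio = true ratio × (1.00 / s)

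| s | no true change | true 20% rise |
|---|---|---|
| 60% | 1.67 | 2.00 |
| 70% | 1.43 | 1.71 |
| 80% | 1.25 | 1.50 |
| 90% | 1.11 | 1.33 |
| 95% | 1.05 | 1.26 |

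An observed ratio near 1.25 fits no true change with s = 80% (1/0.80 = 1.25). It fits a true 20% rise with s = 95% about equally well (1.20/0.95 = 1.26). Even a true 10% fall can appear as a rise: 0.90/0.80 = 1.125. The direction and size of the observed change do not identify the cause.

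**3. How large could the measurement effect be?**

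Inputs from the Introduction: about 50 000 women a year in the UK lose more than 1 L, and about 5000 lose more than 2.5 L. Assume a power-law tail, so that the number above x is proportional to x^(−a).

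a = ln(50 000/5000) / ln(2.5/1) = ln 10 / ln 2.5 = 2.513

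If usual care records a fraction (1 − u) of true loss and quantification records all of it, incidence above any threshold rises by the factor (1/(1 − u))^a with no change in bleeding:

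- u = 5%: (1/0.95)^2.513 = 1.14
- u = 10%: (1/0.90)^2.513 = 1.30
- u = 20%: (1/0.80)^2.513 = 1.75

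The values of u are assumptions, and the tail is fitted to two rounded national figures. The result shows that a modest measurement change could produce a sizeable rise, so the authors' caution is well founded. It also shows that a true rise of 14% to 75% would be indistinguishable from one, so the cause cannot be declared beforehand.

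**The case against.** The sentence closes a limitations paragraph and is not part of the analysis plan. Nothing under Secondary outcomes or Main analysis suppresses, recodes or makes one-sided the analysis of a rise; all four thresholds are to be estimated, and readers will see the results. This stands. A reader might infer that the blood-loss analysis has been fixed so that it can only favour the intervention, or that the trial cannot show harm. The documents do not support that. The primary outcome is RBC transfusion, hysterectomy and maternal death are secondary outcomes, and death and critical care admissions are monitored.

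A reader might also infer an arbitrary asymmetry, since the Introduction reports that "The OBS Cymru intervention was associated with a reduction in massive PPH by 1.10" per 1000 maternities while only a rise is discounted. This too is weaker than it looks. The bias described acts upwards, so a fall would occur despite it, and caution about a rise alone is partly justified. The Introduction also says that the pilot's design did not permit a full evaluation.

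Much of what is needed to interpret a rise is already planned, and further detail may properly sit in the statistical analysis plan, which is not shown. That is accepted: the point is not that a check is missing. It is that the article states a conclusion that such a check could contradict. A published interpretation that predates the results tends to carry into their reporting.

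**Conclusion.** The point holds as a fault in the stated interpretation, not in the analysis. The inference from possible extra detection to no true increase is invalid, and it is weakest in units that quantified loss during usual care. Its reach is the four blood-loss thresholds. The primary outcome and the conclusion on effectiveness are not undermined.

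The documents do not allow the effect to be sized. The illustrative rises of about 14%, 30% and 75% depend on the power-law tail and on assumed under-recording of 5%, 10% and 20%. The detection table depends on assumed sensitivities. The conclusion that a rise alone does not reveal its cause does not depend on these particular values. How many units already quantify loss is not stated.

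**What to change.** Replace the sentence in the Discussion with one saying that an increase in recorded PPH may reflect improved ascertainment, true bleeding or both, and that the cause will not be assumed. State that it will be interpreted using:

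1. The intervention effect on the blood-loss outcomes by whether the unit already quantified loss in usual care, as an extension of the prior-adoption sensitivity analysis in Main analysis. This needs quantification practice at baseline to be recorded; the article does not say whether the context survey at study start covers it.
2. The outcomes least dependent on measured volume: mainly RBC transfusion, with hysterectomy and maternal death as rare supporting outcomes.

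Balloon tamponade, brace suture and level of care should not serve as anchors independent of blood loss. The bundle escalates care at defined measured volumes, so quantification may itself change their use. The individual inclusion criteria also collect PPH-specific data only above 1.5 L or after transfusion, so capture of such outcomes in women not transfused can depend on measured loss (less so for critical care admissions, which Safety considerations says are collected for all participants).

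Allow an explicit conclusion that the cause cannot be determined.

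The cost is one sentence and one stratified analysis. The drawbacks are low precision in the units already quantifying loss and a possibly inconclusive reading.
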